**Fig. 2 Fig2:**
[figure not shown]
Schedule of enrollment, intervention, and assessments. Adverse events, physical examination, AECOPD situation and MMRC, CAT, and TCM symptom scores (TCM symptoms of patients with stable COPD diagnosed with deficiency of lung qi and spleen qi) will be recorded at baseline (week 0) and every 4 weeks during the study period. The 6-min walking distance and BODE will be recorded at weeks 0, 4, 12, 24, 32, and 52. Lung function will be determined at weeks 0, 24, and 52. Safety will be measured at weeks 0, 12, and 24, except for adverse events and physical examination

### Statistical analysis

All data will be analyzed by an independent statistician using SAS 9.4. For all analyses, *P* < 0.05 is considered statistically significant. Measurement data will be presented as number of cases, mean, standard deviation, minimum, median, maximum, upper quartile (Ql), lower quartile (Q3), and 95% confidence interval (95% Cl) data. Paired-sample *t*-test or signed rank sum test will be used to compare the difference between the two groups or pretreatment and posttreatment within one group. Analysis of covariance will be used to compare the differences of center effector other confounding factors.

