### Sample size

A total of 100 patients will be enrolled in this study with 50 in each group. The frequency of AECOPD is the primary outcome. According to previous studies [15, 16], the exacerbation frequency increased 1.17 times each year when receiving conventional medicine, 0.97 times each year when receiving TCM, and 0.68 times each year when receiving both conventional medicine and TCM. Assume that promotional value is achieved only when the exacerbation frequency decreases at least once for each patient every 6 months. The standard deviation (SD) value is 1.25 times per year, the two-sided α is 0. 05, and β is 0. 10. Based on the formula:
$$ \left(\frac{2{\left({\mu}_{\alpha }+{\mu}_{\beta}\right)}^2{\sigma}^2}{\delta^2}\right) $$of the comparison between the means of the two samples, the sample size in each group is 40. Considering a 20% dropout rate over the course of the study, 50 patients will be enrolled in each group and the total sample size will be 100.

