### Screening and run-in, baseline, treatment periods, and endpoint

Adverse events, physical examination, AECOPD situation and MMRC, CAT, and TCM symptom scores will be recorded at baseline (week 0) and every 4 weeks during the study period. The 6-min walking distance and BODE will be recorded at weeks 0, 4, 12, 24, 32, and 52. Lung function will be observed at weeks 0, 24, and 52. Safety will be measured at weeks 0, 12, and 24, not including adverse events and the physical examination. The schedule of assessments and interventions is depicted in Fig. 2.

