In our study, the frequency of acute AECOPD has been chosen as the primary outcome. We also employ validated and objective tools, such as the ACT score and FEV1, as outcome measurements. These measurements improve the reliability and generalizability of the results. Measures will be taken to strengthen quality control. To avoid bias from researchers during this study, an investigator separate from all of the clinical researchers will be hired to preserve and record the randomization information. Therefore, the clinical researchers will not have any input to enrollment or randomization. Also, outcome assessments will be made by an independent clinical statistician blinded to group allocation and not involved in providing intervention or management. We have built a TCM symptom score table to evaluate the TCM symptoms of patients with stable COPD diagnosed with deficiency of lung qi and spleen qi. However, considering the difficulty of recruitment because of the strict inclusion criteria, we have adopted the minimum sample size. Thus, the sample size is a little too small to observe changes in lung function and then show an effect of SHGBZK treatment.

The study has been developed according to the Consolidated Standards of Reporting Trials (CONSORT) [17] statement.

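### Six secondary outcomes are measured at week 0, but the stated between-group test does not adjust for the week-0 value; naming it as an ANCOVA covariate would gain precision at almost no cost

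*Protocol article*

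**What the plan says.** The Statistical analysis section of the protocol article gives the between-group method in one sentence. It offers a paired-sample t-test as the first option and continues with "signed rank sum test will be used to compare the difference between the two groups or pretreatment and posttreatment within one group". The next sentence reads "Analysis of covariance will be used to compare the differences of center effector other confounding factors". The week-0 value of the outcome is not named in either sentence.

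The section on screening, baseline, treatment periods and endpoint sets out when each outcome is measured. MMRC, CAT and TCM symptom score are recorded at week 0 and then every 4 weeks. For the others the text is "The 6-min walking distance and BODE will be recorded at weeks 0, 4, 12, 24, 32, and 52. Lung function will be observed at weeks", and the visits then listed for spirometry include week 0 along with weeks 24 and 52. Six secondary outcomes therefore have a week-0 value of the same quantity.

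Two other places bear on the point. The Lung function subsection treats a positive change from baseline as improvement, which suggests change scores for spirometry. The Discussion concedes that "the sample size is a little too small to observe changes in lung function".

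**The concern.** When an outcome is measured before and after randomisation, a between-group analysis can compare final values, compare changes, or compare final values adjusted for the baseline value (ANCOVA). The third is at least as precise as the other two at any correlation, apart from one degree of freedom. The plan schedules the week-0 values and already includes ANCOVA, but does not connect the two.

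Two things are at stake. First, confidence intervals for the six outcomes will be wider than the collected data allow, in a trial whose authors already call it small for lung function and whose abstract makes exercise capacity part of the hypothesis. Second, a chance difference between arms at week 0 passes into the estimated effect. It pushes the estimate one way if final values are compared and the other way, through regression to the mean, if changes are compared.

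**Working it through.** **Inputs from the protocol.** The allocation is 1:1. Under Sample size, "the two-sided α is 0. 05, and β is 0. 10" and "the sample size in each group is 40", raised to 50 for 20% dropout: 40/(1 − 0.2) = 50. These figures are for the primary outcome; no power, SD or effect size is given for any secondary outcome, so there is no secondary-outcome figure to reproduce.

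The 40 itself does not follow from its stated inputs. With a difference of 1 and an SD of 1.25, the plan's formula gives 2 × (1.960 + 1.282)² × 1.25² / 1² = 32.8, so 33 per group. That is a separate matter. Here 40 serves only as the planned number of completers per arm.

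**Assumptions.** The baseline-to-follow-up correlation ρ is not given; I use 0.3 to 0.8. The starting power is also not given; I use 80%, with 50% and 90% as checks. The calculation treats the between-group test as an ordinary two-sample test of independent arms.

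**Variance of the group difference, relative to comparing final values.**
- Final values: 1
- Change scores: 2(1 − ρ)
- ANCOVA on baseline: 1 − ρ²
- ANCOVA relative to change scores: (1 − ρ²)/[2(1 − ρ)] = (1 + ρ)/2

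**Power.** An unadjusted test with 80% power has a standardised signal of 1.960 + 0.842 = 2.802. With 40 per arm this is an effect of 2.802 × √(2/40) = 0.63 SD. ANCOVA divides the signal by the square root of the variance ratio, so power = Φ(2.802/√ratio − 1.960). For example, at ρ = 0.5 against final values: 2.802/√0.75 = 3.235, and Φ(1.275) = 89.9%.

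| ρ | Ratio to final values | Gain over final values (points) | Ratio to change scores | Gain over change scores (points) |
|---|---|---|---|---|
| 0.3 | 0.91 | 3.6 | 0.65 | 13.5 |
| 0.4 | 0.84 | 6.4 | 0.70 | 11.8 |
| 0.5 | 0.75 | 9.9 | 0.75 | 9.9 |
| 0.6 | 0.64 | 13.8 | 0.80 | 7.9 |
| 0.7 | 0.51 | 17.5 | 0.85 | 6.0 |
| 0.8 | 0.36 | 19.7 | 0.90 | 4.0 |

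Each gain column starts from 80% power for the test it is compared with. Other starting powers, over the same range of ρ:
- From 50%: 3.8 to 40.4 points over final values, 18.1 down to 4.2 over change scores.
- From 90%: 2.5 to 10.0 points over final values, 8.0 down to 2.7 over change scores.

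In terms of interval width, ANCOVA gives √0.91 = 0.95 down to √0.36 = 0.60 of the final-value width, and √0.65 = 0.81 up to √0.90 = 0.95 of the change-score width.

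For spirometry ρ might be nearer 0.9. ANCOVA then has 0.19 of the variance of final values but 0.95 of that of change scores, a gain of only about 2 points from 80%.

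**Chance imbalance.** With 40 per arm the SE of a baseline difference is √(2/40) = 0.224 SD. A difference above 0.3 SD in a given measure has probability about 18% (0.3/0.224 = 1.34); above 0.4 SD, about 7% (0.4/0.224 = 1.79). At ρ = 0.5, a 0.4 SD difference moves a final-value comparison by 0.5 × 0.4 = 0.2 SD, and a change-score comparison by 0.2 − 0.4 = −0.2 SD. Given that imbalance, the final-value test rejects a true null about 10% of the time: the statistic has mean 0.2/0.224 = 0.89 and SD √0.75 = 0.866, against a critical value of 1.99.

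**The case against.** The strongest reply is that this is a condensed article, that a covariate list belongs in a statistical analysis plan not shown here, and that the reference to other confounders could cover the baseline value. Part of this stands: the wording does not exclude baseline. But the article does state its between-group test, and that test does not adjust for baseline. ANCOVA is given a side role, and nothing says which analysis governs. The objection is to the method stated, not to a missing list.

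A second reply is that the difference to be compared may be the change from baseline, as the Lung function subsection suggests. A reader might infer from the test sentence that the week-0 value is ignored altogether; the documents do not support that. Under change scores a gain remains, but it shrinks as the correlation rises, and for spirometry it could be very small. It would also be wrong to conclude that ANCOVA would overcome the sample-size limitation for lung function that the authors concede.

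A third reply is that the plan carries the last observation forward under intention to treat, so 50 per arm may be analysed. This hardly matters: once the starting power is fixed, the gain does not depend on the sample size. At 50 per arm, 80% power corresponds to 2.802 × √(2/50) = 0.56 SD. The imbalance probabilities fall to about 13% (above 0.3 SD) and 5% (above 0.4 SD).

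Finally, a paired test does not suit two independent randomised arms. That is a separate and more basic fault in the same sentence. Switching to an independent two-sample test would still leave the present point open.

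**Conclusion.** The point holds for TCM symptom score, CAT, MMRC grade, 6-min walking distance, BODE and lung function: the stated comparison uses the week-0 value at most through a change score, and a better method is available from data already scheduled. The direction does not depend on the assumed correlation; the size does. From 80% power, with ρ of 0.3 to 0.8, the gain is about 4 to 20 points over final values, or about 14 down to 4 points over change scores. The power figures apply to outcomes treated as continuous and are only a guide for MMRC, which is an ordinal grade.

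Three stronger readings are not supported:
- A reader might take this to cover every secondary outcome. Duration of AECOPD, the interval between onsets and time to first AECOPD have no week-0 value of the same quantity and fall outside it.
- A reader might settle on a single loss of about 10 to 12 points. That needs ρ of about 0.5, which the documents do not give.
- A reader might infer an inflated false-positive rate. The 10% figure is conditional on a 0.4 SD imbalance, which has about a 7% chance at 40 per arm. Averaged over randomisation the unadjusted two-sample test keeps its 5% level.

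This is a loss of precision in secondary outcomes, worth correcting because correction is nearly free.

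**What to change.** Rewrite the between-group sentence in Statistical analysis as follows:
- For TCM symptom score, CAT, 6-min walking distance, BODE and each lung-function measure, compare groups by ANCOVA, or by a mixed model over the scheduled visits. The response is the outcome at the visit; the terms are treatment group, that outcome's own week-0 value and, if there is more than one, centre. Report the adjusted difference with its 95% CI.
- For MMRC, use a proportional-odds model or rank ANCOVA with the week-0 grade as covariate.
- Keep paired tests for within-group description only.

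The cost is a short change of wording and one degree of freedom per outcome for the baseline term. No new data, visits or patients are needed, and ANCOVA is already in the plan. The same rewrite can remove the paired test from the between-group comparison.

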## Methods

### Study design

We will conduct a randomized, double-blind, placebo-controlled trial. A flowchart of the study protocol is shown in Fig. 1.

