### Inclusion criteria

The inclusion criteria are:
The diagnostic criteria in the “Guidelines for the diagnosis and treatment of chronic obstructive pulmonary disease” (2013 revision) [13]Patients with stable symptoms such as cough, sputum production, or breathlessness for 4 weeks with no AECOPDThe risk assessment of AECOPD is high (in the past year, two or more AECOPD occurrences or hospitalized at least once due to AECOPD)TCM syndrome pattern of lung qi and spleen qi deficiency as per the Guidelines for TCM Diagnosis and Treatment of Chronic Obstructive Pulmonary Disease (2011 edition) [14]Aged between 40 and 80 yearsWith informed signed consent and voluntary participation in the study

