### Randomization and masking

#### Randomization

The block randomization method will be used. The appropriate segment length will be selected and SAS9.4 (SAS Institute Inc., Cary, NC, USA) used to generate a randomization sequence for 100 subjects (test group, control group) according to a 1:1 ratio and list the treatment allocation corresponding to serial numbers 001–100 (that is, a random coding table). The placebo is made of SHGBZK Chinese medicine (5%) and dextrin (95%) to ensure it mimics the appearance, smell, and taste of SHGBZK. Both researchers and participants will not know the assignment. The randomization sequence table will be kept in a file. The method, process, group setting, and grouping result of the randomization sequence will be recorded so it can be checked when necessary. Information on intervention assignments will be kept in the third consulting center of biomedical statistics.

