#### Secondary outcome measures

##### AECOPD

Time of first AECOPD occurence, the interval between two onsets of acute exacerbation, the duration of AECOPD, and the severity of AECOPD after the treatment.

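### A paired t-test or signed rank test is specified for comparing two independent randomised arms, so the P value would depend on an arbitrary pairing of patients

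*Protocol article*

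**What the plan says.** The Statistical analysis section of the protocol article covers two different comparisons in one sentence. It opens with the paired-sample t-test and continues, as the alternative: "signed rank sum test will be used to compare the difference between the two groups or pretreatment and posttreatment within one group". The same pair of tests therefore serves the comparison of the arms and the change from before to after treatment within an arm. P < 0.05 "is considered statistically significant" for all analyses, which includes the within-group tests.

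The only other method named is covariance analysis, for a different purpose: "Analysis of covariance will be used to compare the differences of center effector other confounding factors". The section names no independent t-test, rank-sum test or rate model.

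The design is a parallel one. Study design says: "We will conduct a randomized, double-blind, placebo-controlled trial". Randomization describes block randomisation of 100 individually numbered subjects "according to a 1:1 ratio". Neither section describes matching or crossover. The Sample size section uses a formula for comparing the means of two samples.

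Inclusion criteria select patients at high risk: "in the past year, two or more AECOPD occurrences or hospitalized at least once due to AECOPD".

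**The concern.** A paired test works on within-pair differences. That is right for the same patient before and after treatment. It is not right for two groups of different patients, where nothing links a given patient on the formula to a given patient on placebo. An analyst following the sentence literally would have to line up two columns in some order, such as enrolment number or data-set row. Each order gives a different P value for the same data. The main comparison, including that of the primary outcome, would then not be reproducible, and the order would be open to choice. A paired test also needs equal numbers, so any imbalance in the analysed arms means dropping patients.

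A second, smaller matter is the within-group test at P < 0.05. Patients enter because of a bad previous year, so exacerbations may fall afterwards in both arms without any treatment effect. A significant fall from before to after treatment would then say little about the formula.

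**Working it through.** **Inputs.** From the Sample size section: 1.17 exacerbations per year on conventional medicine, 0.68 on conventional medicine plus TCM, SD 1.25 per year, two-sided alpha 0.05, 40 evaluable per arm, 20% dropout. Assumptions of this check: gamma-Poisson counts over one year, with the same dispersion in both arms.

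**1. The plan's own formula is unpaired.** With a difference of 1, 2 × (1.96 + 1.2816)² × 1.25² / 1² = 32.8, so 33 per group. The stated figure of 40 is not reproduced, which is a separate matter. What counts here is the factor 2σ², the variance of a difference between two independent observations. The trial was sized for an unpaired comparison.

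**2. Why the pairing matters.** Both tests have the same numerator, the difference in means. With n per arm, the denominators are:
- unpaired: √[(s₁² + s₂²)/n]
- paired: √[(s₁² + s₂² − 2·r·s₁·s₂)/n]

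Here r is the sample correlation that the chosen row order happens to produce. With unrelated patients it is noise, with standard deviation about 1/√39 = 0.16.

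**3. Numbers.**
- Dispersion: k = (1.25² − 1.17)/1.17² = 0.287.
- Variances: 1.5625 in the control arm and 0.68 + 0.287 × 0.68² = 0.813 in the treated arm (SD 0.90). Their sum is 2.375.
- Unpaired, at a difference of 1.17 − 0.68 = 0.49: t = 0.49/√(2.375/40) = 2.01, 78 df, P = 0.048.
- Paired, r = +0.16: variance 2.375 − 0.361 = 2.015, t = 2.18, 39 df, P = 0.035.
- Paired, r = −0.16: variance 2.375 + 0.361 = 2.736, t = 1.87, 39 df, P = 0.068.

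The same patients with the same outcomes fall on either side of 0.05 through a one-standard-deviation shift in an accidental correlation.

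**4. Simulation, 40 per arm.**

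| Quantity | Result |
|---|---|
| Type I error, paired / unpaired (both arms 1.17) | 4.6% / 4.9%; a second run gave 5.6% / 5.3% |
| Data sets where significance depends on the pairing (1.17 vs 0.68, 200 pairings each) | 33% to 35% |
| Median lowest and highest P over the pairings | 0.013 and 0.096 |
| One arbitrary pairing disagrees with the unpaired test | about 5% of data sets |
| Power at difference 1, SD 1.25 (noncentral t), paired / unpaired | 93.7% / 94.2% |

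**5. Within-group change in exacerbations.** This step takes 1.17 as the mean before selection, whereas steps 3 and 4 take it as the in-trial control rate. The two are separate illustrations. Assume gamma-Poisson counts with mean 1.17 and SD 1.25, entry at two or more past-year events, no true change, and the past-year count as the pretreatment value. The hospitalisation route to entry is not modelled.
- The mean falls from 2.70 to 1.55, and a paired test is significant in about 99% of placebo arms of 40 or 50.
- With assumed means of 0.8 to 2.0 per year and dispersions of 0.1 to 2.0, the share runs from 26% to 100%.

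**The case against.** The strongest defence is that this is a slip of wording in a condensed article. The sample size formula shows that an unpaired comparison was intended, and the term used for the rank test looks like a merger of signed-rank and rank-sum. That may well be so. But the first test named is plainly the paired one, it is assigned to the comparison between groups, and no unpaired two-group test is named elsewhere. A statement that is wrong as it stands is not a detail left to an analysis plan.

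Several stronger readings are tempting and are not supported:
- **That the paired test inflates false positives or costs much power.** It does neither when the pairing is random (step 4).
- **That the result usually turns on the pairing.** One third is the share of data sets in which some pairing changes the conclusion. A single arbitrary pairing differs from the unpaired test in only about 5%.
- **That dropout must lead to discarded patients.** The withdrawal section carries the last observation forward for discontinuers, which could keep the arms equal. Patients are lost only where the analysed numbers differ, as in an analysis of completers.
- **That regression to the mean will make the placebo arm significant.** The protocol does not say that the past-year count is the pretreatment value, nor that within-group results will decide efficacy. Entry also requires four weeks without an exacerbation, so a short look-back at week 0 would not show such a fall. For the symptom, lung function and walking outcomes no such effect is shown: the listed criteria set no severity threshold on these scores, and entry requires a stable state.
- **That the lack of a count model or a survival method for "Time of first AECOPD occurence" is an error in itself.** These may sit in an analysis plan that is not shown, and an unpaired t-test on such counts keeps its type I error near 5%.

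**Conclusion.** The concern holds for the between-group test. As written, the plan assigns paired methods to independent arms, against its own design and its own sample size formula. The harm is an arbitrary P value that cannot be reproduced, with loss of patients if the analysed arms are unequal. The simulated sizes rest on the gamma-Poisson assumption and the protocol's rates and SD. The logical error rests on no assumption.

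The within-group part holds only conditionally: regression to the mean can make a fall in exacerbation frequency significant on placebo if the past-year count is the baseline. The 99% figure should not be quoted without that condition and its range of 26% to 100%.

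**What to change.** Reword the Statistical analysis section before unblinding:

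1. Between groups, name unpaired methods: independent t-test or Wilcoxon rank-sum test or, for continuous outcomes, ANCOVA with the baseline value as covariate.
2. For exacerbation frequency, preferably use a negative binomial model with log follow-up time as offset, reporting the rate ratio and 95% confidence interval. Adjust for the prior-year exacerbation count if that count is recorded; the inclusion criteria state a threshold and do not say that the number itself is kept.
3. Restrict the paired t-test and signed rank test to within-group change, report that change descriptively, and state that it is not evidence of efficacy.

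The cost is a few sentences. These are routine procedures in the planned software. Replacing the paired test with the unpaired one does not raise the sample size: for a difference of 1, SD 1.25 and 90% power, the unpaired t-test needs 34 per group and the paired test with zero correlation needs 35.
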